• Electroconvulsive Therapy (ECT) or ketamine within 12 weeks of enrollment • Current or previously diagnosed psychotic disorder, significant history of mania, or evidence of a personality disorder • Current eating disorder with active purging • Current moderate or severe alcohol or cannabis use disorder within the 12 months prior to enrollment • Active illicit (other than cannabis) or prescription drug substance use disorder at any severity within 12 months prior to enrollment • Current serious suicide risk, as determined through psychiatric interview, responses to C-SSRS, and clinical judgment of the investigator will be excluded; however, history of suicide attempts is not an exclusion • The use of any psychoactive medication not approved by the research team from Baseline through Study Termination (with the exception of gabapentin or certain opiates for pain control) • Positive pregnancy test or breastfeeding. Unable to agree to the use of highly effective contraception methods • History of any medical condition that could make receiving a sympathomimetic drug harmful because of increases in blood pressure and heart rate. This includes, but is not limited to, a history of myocardial infarction, cerebrovascular accident, or aneurysm. Mild, stable chronic medical problems (diabetes mellitus type 2, for example) are allowed in the study if the symptoms from that disease are not being confused with side effects from MDMA or interfering with study participation • Uncontrolled hypertension. Participants with well-controlled hypertension might be enrolled if acceptable cardiovascular risk (family history, smoking, lipid levels, body weight, level of physical activity) and no signs of ongoing cardiovascular or cerebrovascular disease from history, physical exam or ECG supplemented by echocardiography or nuclear imaging, and carotid ultrasound • History of ventricular arrhythmia at any time, other than occasional premature ventricular contractions (PVCs) in the absence of ischemic heart disease • Have a marked Baseline prolongation of QT/QTc interval e.g., repeated demonstration of a QTc interval >450 milliseconds [ms] in males and >460 ms in females (corrected by Fridericia's formula) • Have a history of additional risk factors for Torsade de pointes (e.g., heart failure, hypokalemia, family history of Long QT Syndrome) • Symptomatic liver disease or significant liver enzyme elevation • History of clinically significant hyponatremia or hyperthermia • Weight < 48 kilograms (kg)

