**Figure 1 F1:**
[figure not shown]
Study structure overview.

The preparatory period ends at enrollment confirmation and thus the start of the treatment period. The treatment period lasts approximately 8 weeks and includes two dosing sessions 3-5 weeks apart and three non-drug integrative sessions after each of the two. After the final Integrative Session 2.3 (Visit 12), participants will enter the follow-up period with no study visits for ~4weeks, followed by the Primary Outcome MADRS T2 (Visit 13). The study procedures are presented in Table 2.

**Table 2 T2:** Time and events – study procedures [informed by (35)].

**Time and events – study procedures**	**Screening period (2 to 6 weeks)**			**Preparatory period w/enrollment confirmation** **(2 to 11 weeks)**			
	**Screening**		**Enrollment**	**Preparatory**		**Baseline MADRS T1**	**Baseline & enrollment confirmation**
**Visit**	**Phone screening**	**Screening**	**V0**	**V1**	**V2**	**V3**	**V4**
**Visit description**	**Phone calls**	**In-person visits & labs**	**Enrollment**	**Prep 1**	**Prep 2**	**MADRS T1 assessment at site**	**Prep 3 & enrollment confirmation**
Initial phone screen	✓						
Informed consent	Send Copy	✓					
Follow-up phone screen	✓						
Assess eligibility	✓	✓	✓	✓	✓		✓
Medical/psychiatric history	✓^A^	✓		✓	✓		✓
Past/current medication & adherence	✓	✓		✓	✓		✓
Weight, resting vitals		✓					
Physical exam		✓					
ECG & rhythm strip^H^		✓					
Clinical lab tests		✓					
Drug screen		✓					✓
Pregnancy screen		✓					✓
Enter participant in eCRF		✓					
Record				✓	✓	✓	✓
Medication taper			✓	✓	✓		
Study enrollment			✓				✓ Confirmed
All AEs^B^			✓	✓	✓		✓
90-min preparatory session				✓	✓		✓
Phone call follow-up^C^					✓		
**Time and events – study procedures (continued)**	**Treatment period** ~**8 weeks (**+**/-3 weeks)**								**Follow-up period & study termination (**~**4 weeks)** **13 weeks (**+**/-3 weeks) post baseline**	
	**Treatment 1**				**Treatment 2**				**Outcome**	**Study Termination**
**Visit**	**V5**	**V6**	**V7**	**V8**	**V9**	**V10**	**V11**	**V12**	**V13**	**V14**
**Visit description**	**Exp. 1**	**Int 1.1**	**Int. 1.2**	**Int 1.3**	**Exp. 2**	**Int. 2.1**	**Int 2.2**	**Int 2.3**	**MADRS T2 assessment at site**	**Study termination**
Past/current medication and adherence	✓	✓	✓	✓	✓	✓	✓	✓		✓
Drug screen	✓				✓					
Pregnancy screen	✓				✓					
Record	✓	✓	✓	✓	✓	✓	✓	✓	✓	
All AEs^D^	✓	✓	✓	✓	✓	✓	✓	✓		✓
Administer IP	✓				✓					
8-hour Exp. Session	✓				✓					

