BP, Pulse, Temperature^E^	✓				✓					✓^F^
Overnight Stay	✓				✓					
90-min Integrative Session		✓	✓	✓		✓	✓	✓		
Phone Call Follow-up^G^		✓				✓				
Weight										✓

^A^At Screening, collect data on previous hospitalizations, healthcare utilization and economic productivity. Request participants to obtain medical/psychiatric records to bring to the in-person screening.

^B^All Adverse Events (AEs) includes collecting Serious Adverse Events, AEs of Special Interest, AEs of Psychiatric Status, AEs requiring medical advice or attention, AEs that indicate withdrawal of a participant, and all other AEs.

^C^If needed, call participant to confirm medication tapering and stabilization is complete prior to Visit 3.

^D^All Adverse Events (AEs) includes collecting Serious Adverse Events, AEs of Special Interest, AEs of Psychiatric Status, AEs requiring medical advice or attention, AEs that indicate withdrawal of a participant, and all other AEs.

^E^During Dosing Sessions, vitals are measured before Investigational Product administration, immediately before the supplemental dose is administered (or would be, if supplemental dose not given), and approximately 8 h after initial dose, and as needed.

^F^At Study Termination, only blood pressure needs to be measured.

^G^4 days of phone call follow-up: Day 2 and 7 after the Dosing Session, with two additional calls in between.

^H^We do not repeat the ECGT during the MDMA dosing sessions, since we will avoid possible interference with the therapy facilitated by MDMA.

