#### Safety outcome measures

The C-SSRS is a clinician-administered measure of suicidal behavior designed to detect any suicidal thoughts or behaviors during a clinical trial (51). It consists of a Baseline/Screening version and a Since Last Visit version. The Baseline/Screening version will be administered during screening, and the Since Last Visit version will be used at all subsequent visits. The C-SSRS assesses suicidal ideation, ideation intensity, and behavior.

Safety outcome measures that will evaluate the safety of MDMA-AT in a clinical practice setting are shown in Table 3 [informed by (35)].

**Table 3 T3:** Safety outcome measures.

1. Assess incidence of AEs during Dosing Sessions that may be indicative of a medical complication of the Investigational Product (IP), such as clinical signs and symptoms of chest pain, shortness of breath, or neurological symptoms or any other signs or symptoms that prompt additional vital sign measurements
2. Assess incidence of AEs by severity
3. Assess incidence of Treatment Emergent AEs (TEAEs) by severity
4. Assess incidence of TEAEs by severity taken during a Dosing Session and 2 days after IP administration
5. Assess incidence of AESIs, defined as AEs specified in the protocol related to cardiac function, suicide risk, and abuse liability
6. Assess incidence of AEs by severity categorized as leading to discontinuation of IP, resulting in death or hospitalization, and continuing at Study Termination
7. Assess incidence of SAEs
8. Assess incidence of psychiatric concomitant medications taken during a Dosing Session and 2 days after IP administration
9. Assess incidence of any psychiatric concomitant medications taken during the Treatment Period
10. Assess incidence of serious suicidal ideation and positive suicidal behavior assessed with the Columbia Suicide Severity Rating Scale (C-SSRS)
11. Assess mean changes in blood pressure, heart rate, and body temperature from pre-IP administration to the end of each Dosing Session

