### Adverse events

The sponsor-investigator will pay special attention to the following subset of adverse events (AEs) of special interest (AESIs) – similar as in (35):

a) Cardiac function that could be indicative of QT interval prolongation or cardiac arrhythmias: Torsade de pointes, sudden death, ventricular extrasystoles, ventricular tachycardia, ventricular fibrillation and flutter, syncope (non-postural), and seizures.b) Suicide risk: suicides, suicide attempts, self-injurious behavior associated with suicidal ideation, or severe suicidal ideation (scores of 4 or 5 on the C-SSRS).c) Abuse potential: AEs involving the terms of Behavioral addiction, Drug abuser, Substance abuser, Dependence, Intentional product misuse, Overdose (accidental, intentional, or prescribed), or Drug diversion in cases that are related to MDMA or “Ecstasy.”

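### The only vital-sign safety outcome compares pre-dose with end of session, so the pre-supplement and as-needed readings enter no listed outcome and the acute rise can be understated

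*Protocol article*

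**What the plan says.** The last item of Table 3 (Safety outcome measures, item 11) reads: "Assess mean changes in blood pressure, heart rate, and body temperature from pre-IP administration to the end of each Dosing Session". It is the only listed outcome that summarises vital-sign values.

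The measurement schedule is in footnote E to Table 2. In dosing sessions, "vitals are measured before Investigational Product administration, immediately before the supplemental dose is administered (or would be, if supplemental dose not given"), with a last scheduled reading "approximately 8 h after initial dose, and as needed". Table 2 labels the visit "8-hour Exp. Session", so the end of the session corresponds to the reading at about 8 hours.

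The exclusion criteria in Table 1 show which hazard matters. They exclude conditions that could make "receiving a sympathomimetic drug harmful because of increases in blood pressure and heart rate".

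The Background and rationale section places safety within the primary objective and says that the study is to inform fully powered randomised trials.

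**The concern.** The hazard named in Table 1 is a rise while the drug is acting. A change from pre-dose to about 8 hours shows how far the participant has returned to the starting value by the close of the session. Those are different quantities, and the outcome list contains only the second.

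The trial already takes a reading between the two, and more when needed, but no listed outcome uses those values. A report that follows Table 3 literally could show a small mean change while higher values recorded during the same sessions go unsummarised. With 12 participants, one person's excursion also moves the mean by only one twelfth of its size. Readers planning the next trial would then have a summary of recovery where they need one of exposure to risk.

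**Working it through.** **Step 1. Match readings to outcomes.**

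| Reading (Table 2, footnote E) | Used in Table 3? |
|---|---|
| Before dosing | Yes, item 11 (reference value) |
| Just before the supplemental dose, or when it would have been given | No listed outcome |
| About 8 h after the initial dose | Yes, item 11 (end value) |
| As needed | No listed outcome; item 1 refers to signs that prompt extra readings, but counts adverse events, not values |

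Counting sets of readings if all 12 participants complete both sessions:
- sessions: 12 × 2 = 24;
- scheduled sets: 24 × 3 = 72, of which 24 × 2 = 48 are post-dose;
- post-dose sets used by item 11: 24; unused: 48 − 24 = 24, which is half.

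**Step 2. Direction, without any assumption about the drug.** For participant i in a given session, let E be the change from pre-dose to the end reading, S the change to the pre-supplement reading, and A the change to any as-needed reading. The highest recorded change is M = max(S, E, A). Then E ≤ M for every participant, so mean(E) ≤ mean(M). The two are equal only if every participant's highest recorded value is the end reading.

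**Step 3. Size.** The plan states no figure for this outcome, so there is nothing to reproduce. The article gives no time course for blood pressure or heart rate and no clock time for the supplement. The following is an illustration on assumed inputs only, none of them from the article: effect curve f(t) = ka/(ka − ke) × (exp(−ke·t) − exp(−ka·t)), with ka = ln 2/0.5 h and ke = ln 2/h, where the effect half-life h runs from 1.5 to 8 hours. The pre-supplement reading is at 1.5 or 2.5 hours. A supplement, if given, adds 0.5·f(t − time of supplement).

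One case in full, with h = 1.5 and no supplement: ka = 1.386, ke = 0.462, multiplier 1.5. The peak is at ln(3)/0.924 = 1.19 h, with height 1.5 × (0.577 − 0.192) = 0.577. At 8 h the height is 1.5 × 0.0248 = 0.037. The ratio is 0.037/0.577 = 0.06.

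| Ratio, over all assumed cases | No supplement | With supplement |
|---|---|---|
| End reading / true peak | 0.06 to 0.64 | 0.10 to 0.75 |
| End reading / pre-supplement reading | 0.07 to 0.66 | 0.13 to 1.05 |
| Pre-supplement reading / true peak | 0.74 to 1.00 | 0.67 to 0.77 |

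The end reading is below the true peak in every case. It exceeds the pre-supplement reading only with a supplement and the longest assumed half-life. The pre-supplement reading also misses part of the peak once a supplement is given.

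**Step 4. What a maximum costs.** With no drug effect and independent within-person noise, the expected maximum of two readings lies 1/√π = 0.56 SD above the true mean, and of three readings 3/(2√π) = 0.85 SD. A mean of maxima is therefore biased upwards, more so for participants who have more as-needed readings.

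**The case against.** **The document is a condensed article.** Tables of vital signs by time point are commonly left to the full protocol or analysis plan, and nothing here forbids them. That stands as far as missing tables go. The point is narrower: the article does fix an outcome definition, and that definition omits readings the same article schedules.

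**The wording might mean the whole session.** It could be read as covering everything between the two endpoints. The ordinary reading is a two-point change; if the whole session was meant, the item still needs rewording.

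**Individual excursions have other routes.** Item 1 counts in-session adverse events, items 2 to 4 report events by severity (item 4 for the dosing session and the two days after), and items 6 and 7 cover discontinuation, hospitalisation and serious events. This stands: a rise recorded as an adverse event would be counted. Rises not recorded as adverse events would not be summarised.

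**The shortfall is not certain.** A reader might infer that item 11 must come out below the mid-session value. The documents do not support that. The supplement is given by default, its stated purpose concerns the duration of psychoactive effects, and no haemodynamic time course is given. The pre-supplement reading precedes the second dose, so the end reading could match or slightly exceed it. What stands is the inequality against the highest recorded value.

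**A maximum is not a clean replacement.** It carries upward noise, and as-needed readings are triggered by symptoms and vary in number. This stands, and is why the maximum should be descriptive only.

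**Conclusion.** The point holds in a limited form. Item 11 is the only vital-sign outcome, it uses two of the three scheduled readings, and by construction it cannot exceed the mean of the highest recorded changes. It can therefore understate the acute rise that Table 1 names as the hazard. This rests on the text alone.

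The size is unknown. Under the assumed curves the end reading recovers 6% to 75% of the true peak, but that range reflects the assumptions and is no estimate for this trial.

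A reader might go further and infer that the cardiac events of special interest cannot be trusted, because of footnote H to Table 2 ("We do not repeat the ECGT during the MDMA dosing sessions"). The documents do not support this as a fault of the plan. The choice is disclosed with its reason. The category, introduced as "Cardiac function that could be indicative of QT interval prolongation or cardiac arrhythmias", lists named adverse events and not blood-pressure readings. The article nowhere says that a zero count would show the absence of a QT effect.

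**What to change.** Amend Table 3 item 11 so that, for each dosing session, the change from pre-dose in blood pressure, heart rate and body temperature is reported at each scheduled reading (pre-supplement and about 8 hours). Keep the end-of-session change and label it as a measure of recovery.

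Add a descriptive listing of individual values and the highest recorded value per participant and session. Show the dose received beside each, since Table 4 allows it to differ between participants and sessions, and flag as-needed readings. Twelve participants and two sessions give at most 24 rows, so a listing suits the data better than means split by dose. Make no inference from the maxima, because of their upward noise.

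The cost is slightly more tabulation and a reported vital-sign change that may look less favourable. No new measurement and no change to clinical management is involved.

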#### Exploratory outcome measures

The exploratory outcome measures will explore self-reported depression symptom severity [Beck Depression Inventory II (BDI-II)] (52), quality of life [EuroQol Five Dimensions – Five Levels Questionnaire (EQ-5D-5L)] (53), wellbeing [Warwick Edinburgh Mental Well-being Scale (WEMWBS)] (54), self-compassion [the Self-Compassion Scale (SCS)] (55), alexithymia [the Toronto Alexithymia Scale (TAS-20)] (56), alcohol use [Alcohol Use Disorders Identification Test (AUDIT)] (57) and substance use [Drug Use Disorders Identification Test (DUDIT)] (58). These outcome measures will be assessed during screening and/or at the Baseline visit, and repeated at the Study Termination visit. The BDI-II will also be assessed at visits 8 and 12.

### Study governance and monitoring

The sponsor-investigator will ensure that the quality is maintained throughout the study and will write the study publications.

If new or emerging safety information that affects the benefit/risk assessment of the clinical trial negatively arise, the trial will be discontinued.

The study will be monitored by the Regional Clinical Trial Unit at Oslo University Hospital and the Norwegian Medicines Agency may also want to conduct an inspection. The monitor will get access to source data.

### Adverse events

The sponsor-investigator will pay special attention to the following subset of adverse events (AEs) of special interest (AESIs) – similar as in (35):

a) Cardiac function that could be indicative of QT interval prolongation or cardiac arrhythmias: Torsade de pointes, sudden death, ventricular extrasystoles, ventricular tachycardia, ventricular fibrillation and flutter, syncope (non-postural), and seizures.b) Suicide risk: suicides, suicide attempts, self-injurious behavior associated with suicidal ideation, or severe suicidal ideation (scores of 4 or 5 on the C-SSRS).c) Abuse potential: AEs involving the terms of Behavioral addiction, Drug abuser, Substance abuser, Dependence, Intentional product misuse, Overdose (accidental, intentional, or prescribed), or Drug diversion in cases that are related to MDMA or “Ecstasy.”

### Investigational medicinal product (IMP)

This study will investigate the effects of two open-label MDMA Dosing Sessions of MDMA as described in the table below. Similar MDMA doses to those in the present study have been safely used in previous PTSD trials (28, 30). The dose regimen is shown in Table 4. The rationale of the supplemental dose is to increase the durability of the psychoactive effects.

**Table 4 T4:** Dose regimen of MDMA.

**Dosing session**	**Initial dose**	**Supplemental dose***	**Min-max cumulative dose**
1	80 mg	40 mg	80 mg to 120 mg
2	80 or 120 mg	40 or 60 mg	80 mg to 180 mg
**Total cumulative dose**			160 mg to 300 mg

*Unless tolerability issues emerge with the first dose or the participant declines.

### IMP management

A permit to prescribe MDMA has been obtained from The Norwegian Directorate of Health. MDMA has been supplied by the Multidisciplinary Association for Psychedelic Studies (MAPS). Manufacture and export was performed by SHARP CLINICAL SERVICES, INC., [name]. Good Manufacturing Practice (GMP) has been maintained at all stages of manufacture. All IMP labels will comply with local and national regulations. MDMA will be handled and stored in accordance with all Norwegian regulations. The IMP will be stored and dispensed by the hospital's pharmacy. Study drug treatment will be dispensed at the dosing visit and unused treatments will be re-collected and recorded to verify drug accountability and compliance. At the completion of the study, all unused medicine will be destroyed in accordance with standard safety procedures.

### Long-term follow-up and qualitative interview

At least 3 months after completion of treatment, participants will be invited to a long-term follow-up (LTFU) visit. At the LTFU, a mixed method approach with quantitative and qualitative assessments is taken. We will repeat the same measures as in the outcome (MADRS and SDS) and study termination (BDI-II, EQ-5D-5L, AUDIT, DUDIT, SDS, WEMWBS, TAS-20, BIS, PCL-5, and GAD-7) visits. The LTFU visit also includes a semi-structured interview in which the participants will be invited to explore the perceived experiences with MDMA-AT for MDD. This interview will be transcribed and analyzed with the qualitative method Interpretative Phenomenological Analysis (IPA).

Including a qualitative approach will allow a greater focus on the perspective of the users. There is an insufficient number of qualitative studies exploring participant's experiences of MDMA-AT. To our knowledge, only one qualitative study has explored how participants experience different features of MDMA-AT (59). The main aim of this subproject will be to expand and add nuances to the quantitative measures. This will hopefully broaden our understanding of MDMA-AT for MDD. All included participants will be asked to participate in this qualitative study. A phenomenological/hermeneutic approach will be used to analyze the data. A semi-structured qualitative interview has been developed. This interview will cover the following themes: Experiences with depression, experiences with MDMA-AT, experiences of processes that were helpful and unhelpful, experiences with identity, and experiences with relations to others (family, friends, work, school etc.).

### Dissemination

The results of the study will be published in international peer reviewed journals. The results of the study would also be presented at scientific conferences and in the media.

## Conclusions

Here we have presented a trial protocol for a phase II, proof of principle trial assessing MDMA-AT as a treatment for MDD. This protocol's strength is that it will provide key information about the proof of concept (recruitment, retention and acceptability) in advance of a future definitive study while exploring the safety and the initial impression of treatment efficacy. This study's key limitation is its inability to inform definitive effectiveness of MDMA-AT for MDD, as this is a small, open label pilot trial.

